## 2. Problem Statement and Justification

Patients under mechanical ventilation (MV) in the intensive care unit (ICU) exhibit high hospital mortality rates, ranging from 23% to 51%. This mortality is linked to the success of weaning and the incidence of nosocomial infections. Prolonged MV can increase complications in critically ill patients, extending immobility and raising the risk of ventilator-associated pneumonia, further restricting patients. It is argued that early mobility improves MV-related outcomes, such as ventilator duration and ventilator-free days, breaking the vicious cycle of prolonged MV and immobilization. Additionally, early rehabilitation is associated with reduced morbidity and mortality, as well as complications of the disease, ICU length of stay, hospital stay, and rehospitalization rate. Therefore, weaning from MV through early rehabilitation is crucial to improving the prognosis of ICU patients.

Despite the growing evidence on the utility of early rehabilitation for critically ill patients, programs and interest in outcomes vary among studies. Given this diversity, healthcare professionals must assess whether different programs have a similar therapeutic effect and ensure that the prescribed rehabilitation provides benefits consistent with previous literature. Besides the heterogeneity among programs, different countries and institutions face barriers to implementation, such as a shortage of trained rehabilitation personnel and a cultural gap in the ICU. In cases of personnel

shortages and settings with conservative ICU ethics, early rehabilitation is adapted to a sustainable level, including modified programs or less frequent visits.

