## 6.6. Outcomes

### *Effectiveness*

Main outcome: time (days) from intubation to extubating.

- Secondary outcomes:

- Days free of mechanical ventilation until day 28
- Days of delirium until day 28
- Time in ICU with delirium until day 28
- Days of hospitalization with delirium until day 28
- Days of sedation until day 28
- Sedation-free days until day 28
- Extubating failure
- Need for non-invasive mechanical ventilation
- Exploratory outcomes:
- Barthel index at discharge
- Days of hospital stay
- Length of stay in ICU
- Mortality from any cause up to 90 days
- Time from intubation to start of therapy
- Muscular strength measured with the Medical Research Council (MRC) scale
- Dysphagia 72 hours after extubation
- Dysphonia 72 hours after extubation
- Time until initiation of oral administration post-extubation
- Development of healthcare-associated pneumonia,
- Maximum mobility measured by JH-HLM
- Grip strength
- Cognitive function measured using the Montreal Cognitive Assessment (MOCA)
- Evaluation of functionality in daily activities until day 28
- Quick sensitivity and dexterity test

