After the observation phase, essential data related to the patient's functionality and hospital stay will be collected. The Barthel Index at hospital discharge, cognitive function measured by the Montreal Cognitive Assessment (MOCA), and the quick sensitivity and dexterity test will be recorded, providing a detailed measure of the functional and cognitive capacity achieved. Additionally, the days of hospital stay and the length of stay in the Intensive Care Unit (ICU) will be documented, offering insights into the duration of the recovery process. Mortality will be evaluated, indicating whether it occurred during the observation period. Furthermore, functional independence will be measured using Activities of Daily Living (ADLs) at hospital discharge and ICU discharge, providing a comprehensive assessment of the impact of care and procedures on the patient's autonomy (see Annex 3 and 4).

Within the protocol, the inclusion of safety variables such as blood pressure alteration, cardiac arrhythmias, and oxygen desaturation highlights the importance of continuous monitoring of cardiovascular and respiratory health in patients. These variables serve as key markers to identify potential complications during the intervention or medical treatment. Early detection of blood pressure alterations provides crucial insights into perfusion and circulatory function. Monitoring cardiac arrhythmias aims to identify irregularities in heart rhythm while observing oxygen desaturation alerts to potential issues in tissue oxygenation. These safety measures, integrated into the protocol, contribute to a comprehensive evaluation and proactive management of any changes in the patient's condition, thereby supporting safety and well-being during the clinical process.

[figure not shown]

**Figure 1.** Study design diagram

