| Days from the start of ventilatory support to the start of weaning | Days from the start of ventilatory support (intubation) to the start of weaning                                                                                                                   | Discrete Quantitative   | Days                                                                                                                                                                                                     |
| Days of mechanical ventilation                                     | Days of invasive mechanical ventilation                                                                                                                                                           | Discrete Quantitative   | Days                                                                                                                                                                                                     |
| Days free of mechanical ventilation                                | 28 days minus ventilation days                                                                                                                                                                    | Discrete Quantitative   | Days

It will be defined as 0 if the patient dies or has been ventilated for more than 28 days.                                                                                                    |
| Delirium                                                           | For a patient to be considered to have delirium according to the CAM-ICU, both the first criterion (acute alteration in mental status) and at least one of the other three criteria (inability to | Qualitative Nominal     | 
 
1. Acute alteration of mental status (+/-).
 
2. Inability to maintain sustained attention (+/-).
 
3. Disorganization of thought (+/-).
 
 |

|                                          |                                                                                                                                |                       |                                                        |
|------------------------------------------|--------------------------------------------------------------------------------------------------------------------------------|-----------------------|--------------------------------------------------------|

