|                                          | maintain sustained attention, disorganization of thought, or fluctuating changes in level of consciousness).                   |                       | 4. Fluctuating changes in level of consciousness (+/-) |
| Days of delirium                         | Days with the presence of delirium                                                                                             | Discrete Quantitative | Days                                                   |
| Sedation days                            | Days with sedation                                                                                                             | Discrete Quantitative | Days                                                   |
| Sedation-free days                       | 28 days fewer days of sedation                                                                                                 | Discrete Quantitative | Days
It will be defined as 0 if the patient dies.   |
| Barthel index at hospital discharge      | The Barthel Index is a scale used to measure a person's degree of functional independence in activities of daily living (ADL). | Discrete Quantitative | It will be 0 if the patient dies.                      |
| Days of hospital stay                    | Days of hospital stay                                                                                                          | Discrete Quantitative | Days                                                   |
| Days of ICU stay                         | Days of ICU stay                                                                                                               | Discrete Quantitative | Days                                                   |
| Mortality                                | Death                                                                                                                          | Qualitative Nominal   | Yes or no                                              |
| Time from intubation to start of therapy | Time from intubation to start of therapy                                                                                       | Discrete Quantitative | Days                                                   |

Association between early multimodal therapy and days of mechanical ventilation in the intensive care unit of the Fundación Santa Fe de Bogotá: A randomized controlled clinical trial.

Version 6.0

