### 6.13. Statistical Analysis Plan

A Shapiro-Wilk test will be conducted to verify the distribution of quantitative variables, considering the number of patients included. Data will be presented as means or medians, accompanied by their standard deviation or interquartile range, as appropriate. Categorical variables will be described as absolute and relative frequencies.

To compare continuous variables between the two groups (early vs. late therapy), a T-test or the Mann-Whitney U test will be employed, depending on the distribution of the data. For categorical variables, a  $\chi^2$  test or Fisher's exact test will be used, as appropriate.

The primary objective of the study is to evaluate the association between the use of early multimodal therapy and the days of invasive mechanical ventilation. To address this question, we will perform a survival analysis and a Cox regression. A risk variable will be created by combining the time of invasive mechanical ventilation and extubation (yes/no). Then, a univariable Cox regression analysis will be performed with the risk variable as the dependent variable and the intervention group (early vs. late) as the independent variable. Additionally, a survival curve will be generated, and differences between the two groups will be analyzed using a log-rank test.

To evaluate factors related to the time of mechanical ventilation, univariable Cox regression models will be performed for all variables included in the study. To determine whether continuous variables can be evaluated continuously or as categorical variables, the assumption of linearity will be checked through the Martingale residual plot. If linearity is not met, the variable will be stratified, and cut-off points will be defined according to the appearance of the plot. Subsequently, those variables with a statistically significant p-value (less than 0.25) and clinically important variables (age, sex, delirium, etc.) will be included in a multivariable Cox regression model. The best model will be selected through a Backward Stepwise process based on Akaike (AIC) and Bayesian (BIC) information criteria.

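### Hospital and ICU stay are plain day counts with no rule for death, so a between-arm difference cannot be read as duration of recovery

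*Protocol*

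**What the plan says.** Both stays are listed as outcomes. The PICOT table in section 3 puts them among the secondary outcomes; section 6.6 puts them, for example "Length of stay in ICU", under the exploratory ones.

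The variable table in 6.11 gives the rows "Days of hospital stay" and "Days of ICU stay". Each is defined by its own name, as a discrete quantity in days. Neither row says what value a patient who dies receives.

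Other rows of the table do have such a rule. For ventilator-free days, "It will be defined as 0 if the patient dies or has been ventilated for more than 28 days". For sedation-free days, "It will be defined as 0 if the patient dies". Barthel at discharge, JH-HLM mobility and grip strength are also set to 0 at death.

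For continuous variables compared between arms, 6.13 says that "a T-test or the Mann-Whitney U test will be employed, depending on the distribution of the data". Sections 6.1 and 6.8 analyse all randomised patients as assigned. Section 6.7 gives the reading: "length of stay in the Intensive Care Unit (ICU) will be documented, offering insights into the duration of the recovery process". Section 2 states that ventilated ICU patients "exhibit high hospital mortality rates, ranging from 23% to 51" per cent.

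The data form in Annex 5 (final observation) annotates hospital stay with the day on which the intensivist announces transfer to the ward. That day ends the ICU stay, not the hospital stay.

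**The concern.** A stay can end because the patient recovered or because the patient died. A plain day count treats the two alike, and a two-sample test on all randomised patients then compares a mixture. Section 6.7 says that the result informs how long recovery took, which the mixture cannot show.

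At the mortality quoted in section 2, a quarter to a half of the values could be times to death. If the arms differ in mortality, stay can differ between them when survivors recover at exactly the same pace. A shorter stay might be reported as a benefit when it reflects deaths. Depending on when deaths occur, a longer stay might equally reflect deaths and not slower recovery.

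**Working it through.** The plan states no figure for stay, so there is none to reproduce. The check asks how large a spurious difference could be when survivors' stay is identical in both arms.

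**Inputs from the protocol.** 37 patients per arm (6.4). Hospital mortality 23% to 51% (section 2). I take 23% in one arm, and either 37% (the middle of the range) or 51% (its upper end) in the other.

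**Assumptions, not in the protocol.** Survivors' stay is lognormal with median 15 days and log-SD 0.6. Time to death is lognormal with log-SD 0.8 and median 5, 10, 15 or 20 days.

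**Difference in mean stay.** A lognormal mean is median × exp(SD²/2).

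- Survivors: 15 × exp(0.18) = 17.96 days.
- Deaths: median × exp(0.32) = median × 1.377.
- Spurious difference, higher-mortality arm minus the other: (difference in mortality) × (mean time to death − 17.96).

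| Median time to death | Mean time to death | 37% v 23% (× 0.14) | 51% v 23% (× 0.28) |
|---|---|---|---|
| 5 days | 6.89 | −1.55 | −3.10 |
| 10 days | 13.77 | −0.59 | −1.17 |
| 15 days | 20.66 | +0.38 | +0.76 |
| 20 days | 27.54 | +1.34 | +2.68 |

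The sign changes where median × 1.377 = 17.96, that is, at a median time to death of about 13 days under these assumptions.

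**How often a test would mislead.** Trials simulated on the same model with 37 per arm and a two-sided Mann-Whitney test at 0.05 gave a significantly shorter stay in the higher-mortality arm in 4–11% of trials at 37% v 23%, and in 8–33% at 51% v 23%, for death medians of 5 to 10 days. The nominal rate is 2.5%. At a death median of 15 days the rate is about 2–3%, which is no excess.

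**A second set of assumptions.** Survivor median 10 days, log-SD 0.6 for both survivors and deaths. The difference is (difference in mortality) × (death median − 10) × 1.197.

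- Death median 3 days: 0.14 × (−7) × 1.197 = −1.17 days, and −2.35 days with 0.28.
- Death median 10 days: 0.
- Death median 15 days: +0.84 and +1.68 days.

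The pattern is the same.

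**Free days with death scored 0.** In the first model, hospital-free days to day 28 average 28 × Φ(1.040) − 17.96 × Φ(0.440) = 28 × 0.8509 − 17.96 × 0.6701 = 11.79 among survivors, where 1.040 = ln(28/15)/0.6 and 0.440 = 1.040 − 0.6. Deaths contribute 0. The higher-mortality arm is therefore worse by 0.14 × 11.79 = 1.65 days or 0.28 × 11.79 = 3.30 days, whatever the timing of deaths. The sign no longer depends on an unknown.

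**The case against.** Several objections have force.

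- **That the stay ends at death is an inference.** The protocol does not say so. A reader might infer that a patient who dies on day 3 is recorded with the best possible value, but the documents do not state this. On the Annex 5 form, a patient who dies in the ICU has no announced transfer to the ward, so hospital stay would be undefined. This stands. It shows that the value for such patients is not fixed; it does not make the intended reading safe.
- **The omission is not peculiar to stay.** Days of ventilation, sedation and delirium are also plain counts without a death rule. Ventilation and sedation have free-day companions that score death; delirium has none. So the table does not single stay out. This stands, but it does not help the two stay outcomes.
- **The test sentence in 6.13 is generic and does not name stay, and detail may be left to a statistical analysis plan.** True. Even so, the protocol itself gives the variable definition, the general comparison, the analysis set and the interpretation, and followed as written these lead to the problem.
- **Mortality is reported separately.** It is, to 90 days. At 51% v 23% a Fisher test on mortality would itself be significant in about 62% of trials, so readers would often be warned. At smaller gaps the warning is weaker, but so is the bias.
- **The size depends on assumptions.** The 23–51% is a background range, not an expected gap between arms, and the eligibility criteria exclude some high-risk patients. The 51% v 23% contrast is extreme.

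**Conclusion.** The point holds as one of interpretation: with a plain day count and no rule for death, a between-arm difference in hospital or ICU stay cannot be read as duration of recovery.

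Under the 15-day survivor median, with deaths at a median of 5 to 10 days, the arm with more deaths has a mean stay about 0.6 to 1.6 days shorter at 37% v 23% mortality, and about 1.2 to 3 days shorter at the extreme of 51% v 23%. With deaths at a median of 15 to 20 days, its mean stay is about 0.4 to 2.7 days longer.

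A reader might infer that a harmful treatment would always appear to shorten stay. The documents do not support that. They give no timing of deaths, and the bias vanishes or reverses when deaths come around or after the usual discharge time.

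The outcomes are exploratory in 6.6, although secondary in the PICOT table, and the primary outcome is untouched. The change is worth making because it is cheap and because 6.7 states the reading that the data cannot bear.

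**What to change.** In 6.6, 6.11 and 6.13, make the between-arm comparison one of these:

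- ICU-free and hospital-free days to day 28, with death by day 28 scored 0, the convention already used for ventilator-free days; or
- time to discharge alive, from the ICU and from hospital, with death as a competing event.

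Show raw days of stay only descriptively, separately for survivors and non-survivors, and change the sentence in 6.7 to match.

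In the same edit, reconcile the Annex 5 annotation for hospital stay with hospital discharge. Until that is done, no hospital-stay measure can be computed reliably.

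The cost is mainly wording. Admission date, discharge date and days to death are already listed for collection. The form has a single discharge date and does not say which discharge it means, so ICU and hospital dates should be recorded separately. The downside is that the result is no longer a plain mean number of days; free days combine mortality with stay and should be described that way.

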### Discontinuation of therapy

The intervention will be interrupted in any of the following clinical contexts:

- The patient leaves the ICU before completing 24 hours with invasive ventilatory support through an orotracheal tube.
- Death of the patient during their stay in the ICU (up to 28 days)
- The treating physician determines that considering the best interest of the patient it is best to discontinue her participation in the study
- Withdrawal of informed consent by the patient or legal representative

Following the interruption of treatment, the medical management of the patient will continue with the standardized treatments and therapies of the intensive care unit. Treatment may be temporarily interrupted due to medical reasons, which include but are not limited to surgical procedures, radiology studies, and hemodynamic stabilization of the patient. Multimodal therapy will be resumed as soon as possible.

### 6.8 Losses and Handling of Missing data

- Frequency and Distribution: Losses during follow-up were recorded for participants in both study groups. Of [total number of participants] initially assigned, [number of participants lost] were lost during the study period.
- Reasons for Losses:
  - o Voluntary withdrawal of consent by the participant.
  - o Adverse events not related to the study treatment.
  - o Failure to comply with the study protocol.
  - o Transfer to other medical facilities.
- Comparison between Groups: A comparative analysis will be carried out between the control and intervention groups, to assess the equitable distribution of losses.
- Characteristics of Lost Participants: The baseline demographic and clinical characteristics of participants who completed the study will be compared with those who were lost to follow, to assess whether the losses introduced substantial biases.

- **Impact on Analysis:** A sensitivity analysis will be performed to evaluate the potential impact of losses on the study results. Results will be presented with both the inclusion and exclusion of missing participants.

- **Statistical Management:** In the main statistical analysis, the intention-to-treat approach will be used, including all participants according to their original assignment, regardless of their compliance or loss to follow-up. We will also perform a sensitivity analysis based on a per-protocol analysis since it could provide us with a measure of the effect of weaning under ideal treatment adherence conditions.

- **Replacement of Lost Participants:**

- o **Ethical Consideration:** Before considering the replacement of lost participants, an ethical evaluation of the justification for such action will be conducted. It will be considered whether the replacement is ethically acceptable and whether its implementation respects the rights and well-being of the participants.

- o **Imputation Methods:** If replacement of lost participants is considered, statistically sound and well-founded imputation methods will be used. Options such as imputation by the mean, LOCF, or other more advanced methods such as multiple imputation will be explored.

- o **Transparency and Documentation:** A detailed description of the imputation methods used will be provided, including the reasons for choosing a specific method. This will be included in the final reports and communication with the Ethics Committee.

- o **Report to the Ethics Committee:** The report to the Ethics Committee will describe in detail any participant losses and any decisions related to the replacement of missing data. Transparency in loss management and consistency with the original study protocol will be emphasized.

- o **Expert Consideration:** The opinion of experts in statistics and research ethics will be sought to ensure that any decisions related to loss management and replacement of lost participants are informed and ethical.

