### 6.3. Sample size

Based on the study published by Schweickert et al. where they found that the mean number of days of mechanical ventilation in patients with usual physical therapy was  $6.1 \pm 1.4$  days and in early therapy it was  $3.4 \pm 1.25$  days (32), for an alpha error of 0.05 and a statistical power of 0.8 is considered the following formula:

$$ES = \frac{|\mu_1 - \mu_2|}{\sqrt{DE1^2 - DE2^2/2}}$$

$$ES = \frac{|6.1 - 3.4|}{\sqrt{1.40^2 - 1.25^2/2}}$$

$$ES = \frac{2.7}{\sqrt{3.52/2}}$$

$$ES = 2.03$$

With the effect size calculated ( $ES \approx 0.4463$ ), we can use the formula for the sample size mentioned earlier:

$$n = \frac{2 \left( \frac{Z\alpha}{2} + Z\beta \right)^2 \cdot (\sigma_1^2 + \sigma_2^2)}{ES^2}$$

Where  $\frac{Z\alpha}{2}$  is the critical value corresponding to the alpha significance level /2 to  $\alpha = 0.025$ ,  $\frac{Z\alpha}{2} \approx 2.81$

and  $Z\beta$  is the critical value corresponding to the statistical power beta to  $\beta = 0.90$ ,  $Z\beta \approx 1.28$

The other values we have are the same:

- Mean of group 1 ( $\mu_1$ ) = 6.1 days
- Standard deviation of group 1 ( $\sigma_1$ ) = 1.4 days
- Mean of group 2 ( $\mu_2$ ) = 3.4 days
- Standard deviation of group 2 ( $\sigma_2$ ) = 1.25 days

Effect size ( $ES$ )  $\approx 20.03$  (previously calculated)

Substituting these values into the formula:

$$n = \frac{2 (2.81 + 1.28)^2 \cdot ((1.40)^2 + (1.25)^2)}{(2.03)^2}$$

$$n = \frac{2 (4.09)^2 \cdot (1.96 + 1.56)}{4.13}$$

$$n = \frac{2 (16.72) \cdot (3.52)}{4.13}$$

$$n = \frac{(35.35) \cdot (3.52)}{4.14}$$

$$n = 30.29$$

Rounding:

$$n = 31 \text{ by each group}$$

To the estimated 31 patients per arm, an extra 20% (6 patients per arm) is added to minimize the loss of statistical power in case patients withdraw from the study or there are missing data.

The sample size has also been determined based on the magnitude of the expected effect of mobilization within 48-72 hours of mechanical ventilation, as suggested in the reference study (33), which justifies our choice to evaluate early mobilization at 24 hours versus 72 hours after mechanical ventilation in our study.

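### Section 6.8 leaves mean imputation and LOCF open for a censorable duration outcome and for running day counts, where each can distort the comparison in its own way

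*Protocol*

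**What the plan says.** Section 6.8 of the Protocol commits the main analysis to intention to treat, with every participant included whether or not lost. Under its item on replacing lost participants it then says: "If replacement of lost participants is considered, statistically sound and well-founded imputation methods will be used". The next sentence names the candidates: "Options such as imputation by the mean, LOCF, or other more advanced methods such as multiple imputation will be explored". The method used and the reasons for it are to appear in the final reports.

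Three other places bear on this:

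- Section 6.3 has already enlarged the sample for losses: "To the estimated 31 patients per arm, an extra 20% (6 patients per arm) is added to minimize the loss of statistical power".
- Section 6.6 defines the main outcome as days from intubation to extubation. Section 6.13 analyses it by Cox regression and log-rank test on ventilation time combined with extubation status, and compares continuous variables by t-test or Mann-Whitney test.
- The variable table in section 6.11 defines ventilator-free days as "28 days minus ventilation days". It sets the value to 0 for death or for ventilation beyond 28 days, and has no rule for a patient lost while still ventilated.

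Section 6.13 contains no missing-data rule that would override section 6.8.

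**The concern.** Days of ventilation, sedation and delirium accumulate while the patient is under observation. The last recorded value of such a count is a lower bound, not an estimate of the final value. Carried forward, it turns early departure into a favourable result. A patient transferred on day 4 while ventilated would be recorded with 4 ventilation days and 28 - 4 = 24 ventilator-free days.

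The reasons for loss in section 6.8 (unrelated adverse events, non-compliance, transfer) and the withdrawal criteria in section 6.2 could remove sicker patients who are still ventilated. Section 6.1 says participants and researchers know the arm. Unequal loss is therefore plausible, and under LOCF the arm that loses more ventilated patients would appear to do better.

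Mean imputation raises a different problem. It adds records that carry no information, and the test counts them as real. If the mean is taken within each arm, the standard error comes out too small even when losses are random.

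The clause also treats imputing data as a form of replacing participants, which confuses two separate decisions.

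**Working it through.** **The plan's own figure.** Section 6.3: 20% of 31 is 6.2, taken as 6, and 31 + 6 = 37 per arm. This reproduces. As a share of those randomised the allowance is 6/37 = 16.2%.

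**Mean imputation within arm.** Take 31 observed and 6 imputed per arm. The sum of squares is unchanged, but it is divided by 36 instead of 30, and the sample is counted as 37 instead of 31.

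- Ratio of naive to true standard error = sqrt(30/36) x sqrt(31/37) = 0.913 x 0.915 = 0.836.
- Two-sided error at nominal 5% = 2 x (1 - Phi(1.96 x 0.836)) = 2 x (1 - Phi(1.64)) = about 10%.
- A simulated t-test with exactly 6 imputed per arm (20,000 runs) gave 9.85%.
- With 20% lost, the approximation 2 x (1 - Phi(1.96 x 0.80)) gives 11.7%.

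**Simulation under no treatment effect.** 37 per arm; 2,000 runs per scenario; normal, shifted-exponential and lognormal ventilation times; losses while ventilated and unrelated to total duration. Ranges are across the three distributions.

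| Handling, 16.2% lost per arm | t-test | Mann-Whitney | log-rank |
|---|---|---|---|
| Within-arm mean, imputed values counted as extubations | 8.4-9.0% | 12.0-12.4% | 9.7-13.0% |
| Overall mean | 4.0-4.2% | 3.9-4.1% | 4.4-5.0% |
| LOCF taken as completed ventilation | 1.2-3.6% | 1.8-3.6% | 3.2-4.4% |
| Censored at last observation | - | - | 4.3-4.4% |

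At 20% lost per arm, within-arm mean imputation gave 10.4-16.7% across the tests. Censoring stayed within 4.3-5.4% over both loss rates.

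**LOCF with unequal losses.** Assume 30% lost in the early arm and 10% in the late arm. LOCF then produced a false difference of 0.56 to 0.58 days in favour of the early arm. The t-test error was 7.2% (exponential) and 19.5% (normal). Log-rank with censoring gave 6.8% and 5.8% in the same two scenarios, so it was much less affected than the LOCF t-test under normal times, but only slightly less under exponential times.

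**Size of the LOCF shift.** If 6 of 37 in one arm only are lost while ventilated, each with r days still to come, that arm's mean falls by 6r/37:

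- r = 3: 0.49 days, 18% of the 2.7-day planning difference (6.1 - 3.4).
- r = 6: 0.97 days, 36%.
- r = 10: 1.62 days, 60%.

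The value of r is an assumption. On section 6.3's figures, a total above 10 days lies (10 - 6.1)/1.4 = 2.8 SD above the late-arm mean and (10 - 3.4)/1.25 = 5.3 SD above the early-arm mean, so r = 10 does not fit the plan's own inputs. If loss falls on average halfway through a 6.1-day course, r is about 3.

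**The case against.** The best defence is that the clause is conditional, demands sound methods and also lists multiple imputation. Section 6.8 promises results with and without the missing participants, a comparison of losses between arms and expert statistical advice. Section 6.1 blinds the statisticians to the groups, which limits any choice of method by its result. The time-plus-status variable of section 6.13 already allows a patient lost while ventilated to be censored, and carrying forward both the day and the not-extubated status would be the same thing. The 6 per arm cover withdrawals and missing data of every kind, and some losses will come after extubation, when the primary outcome is known. A separate analysis plan may settle the details.

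Most of this stands and limits the point, but it does not remove it. The Protocol goes beyond leaving the method open: it names two unsuitable ones. Section 6.8 never ties losses to the censoring in section 6.13. The t-test and Mann-Whitney comparisons of day counts have no such protection.

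A reader might infer that one practice both shortens the recorded ventilation and doubles the false-positive rate. The calculations do not support that. Short scoring belongs to LOCF, which did not inflate the error with equal losses. The doubling belongs to within-arm mean imputation; the overall mean does not cause it, and section 6.8 does not say which mean is meant. Nor should the 60% shift be read as a forecast: it needs every loss in one arm and a duration that the planning SDs make very unlikely.

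**Conclusion.** The point holds in a limited form. Section 6.8 accepts two single-imputation methods that do not suit a censorable time to extubation or running day counts.

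- **LOCF on day counts** biases the comparison when losses during ventilation differ by arm. Under an assumed 30% against 10% loss, the false difference is about 0.6 days. The documents give no loss rates by arm, so the actual size is unknown.
- **Within-arm mean imputation** raises a two-sided 5% error to about 10% by formula, and to about 8-13% in simulation. This assumes that the whole allowance of 6 of 37 per arm is imputed and that losses are random.

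The documents do not show that the primary analysis will be affected. They leave that possible, because they do not say that losses are censored.

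**What to change.** In section 6.8:

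1. Delete mean imputation and LOCF for the duration and day-count outcomes.
2. State that in the Cox and log-rank analyses of section 6.13 a patient lost while ventilated is censored at the last day known ventilated, with no imputed extubation.
3. Use multiple imputation for the day-28 counts, with imputed values no lower than the days already observed.
4. Add a sensitivity analysis that treats patients lost while ventilated as ventilated to day 28, because the censoring may be informative.
5. Separate replacing participants from imputing data. Section 6.3 already added 6 per arm "to minimize the loss of statistical power in case patients withdraw from the study or there are missing data", so any further replacement needs its own justification.

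The cost is a wording change and a little more analysis work. Confidence intervals will be somewhat wider than under single imputation.
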